#### Control group

Patients who do not want to take part in the mHealth intervention will be assigned to the control group. In addition, there are three other obesity centres that do not offer an mHealth intervention from which patients will be recruited. In these centres, patients have their first stay in an obesity centre organized by groups with about twelve patients. During this stay, there are individual and group sessions with a focus on nutritional therapy and exercise therapy. When leaving the obesity centre, the patients will receive an exercise plan and dietary recommendations that should help them implement what they have learnt at the obesity centre. Equal to the intervention groups, all patients can receive additional therapies depending on their health status.

It is important to note that for logistical reasons, the involved obesity centres have differences regarding the type of intervention. While in two of the obesity centres the first stay of the patients lasts three weeks, in one centre the first stay lasts one week. In addition, two of the obesity centres offer two additional stays, while one offers no additional stay.

#### Data collection

This study consists of quantitative as well as qualitative data collection methods.

##### Quantitative data collection methods

The data collection will start in July 2021 and the recruitment of patients for the baseline measurement is planned to finish in May 2022. The data collection will include three measurements (see Fig. 1). For all patients, the baseline measurement will take place during the first stay at the obesity centre. The follow-up measurements are aligned with the patients’ stays in the intervention group. For patients from obesity centres who offer an mHealth intervention, the first follow-up measurement will take place during the second stay at an obesity centre and the second follow-up measurement during the third stay. Patients recruited from obesity centres that do not offer an mHealth intervention will have the first follow-up measurement after six and the second follow-up measurement after twelve months, with the questionnaires directly sent to them. Questionnaires will also be sent directly to patients who are in obesity centres that offer an mHealth intervention (and thus potentially include further stays at the obesity centre), but do not attend them (e.g., due to weight gain, another stay was not approved by the insurance provider). Depending on the patients’ preference, the questionnaires will be sent either by e-mail or by post and a reminder will be sent if the patients do not return the questionnaires within two weeks.

**Fig. 1 Fig1:**
[figure not shown]
Study design

Demographic information, including age, gender and current employment situation, will be asked at baseline. All other instruments described below will be used at the baseline measurement and the two follow-up measurements. The SPIRIT timetable of the study is presented in Fig. 2.

**Fig. 2 Fig2:**
[figure not shown]
SPIRIT timetable

#### Body weight

The body weight will be provided by the obesity centres if the patients agree that this information can be forwarded. In case the patients are not at the obesity centre during the measurement, the patients will be asked to report their weight themselves. The patients will be asked to wear light clothing and no shoes during the measurement and to report their weight to the nearest 0.1 kg.

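### Follow-up weight comes from the centre for some patients and from self-report for others, unequally between groups and partly depending on the outcome, so reporting error enters the group-by-time contrast

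*Protocol article*

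**What the plan says.** The protocol article sets the place of measurement under Quantitative data collection methods. Baseline is common to all: "For all patients, the baseline measurement will take place during the first stay at the obesity centre". Follow-up is organised by type of centre. The general rule reads: "The follow-up measurements are aligned with the patients’ stays in the intervention group". Where a centre runs the mHealth programme, the rule is: "the first follow-up measurement will take place during the second stay at an obesity centre and the second follow-up measurement during the third stay". By contrast, patients of centres without it "will have the first follow-up measurement after six and the second follow-up measurement after twelve months, with the questionnaires directly sent to them". The same section adds that mHealth-centre patients who do not attend a further stay are also sent the questionnaire, and it names weight gain as one reason for not attending.

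The Body weight section sets the source. At the centre: "The body weight will be provided by the obesity centres if the patients agree that this information can be forwarded". Elsewhere: "In case the patients are not at the obesity centre during the measurement, the patients will be asked to report their weight themselves".

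Three other places matter. The section on the mHealth obesity intervention makes absence of weight gain since the last stay a criterion for another stay. The Control group section says of the three control centres that "two of the obesity centres offer two additional stays, while one offers no additional stay". Data analysis of quantitative data tests weight in a repeated-measures MANOVA with two groups and three time points. Its listed covariates are age, gender, frequency of app use and outside physical activity; weight source and centre are not among them.

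**The concern.** If self-reported weight differs systematically from weight supplied by the centre, a patient who moves from one source at baseline to the other at follow-up shows an apparent change that is not real. This does no harm to the comparison if both groups move equally. Here they need not: control-centre patients can only be controls, and the text follows them remotely at both later waves, while attending mHealth-centre patients stay on centre weights.

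The source also depends on the outcome. Within mHealth centres, patients who gained weight are among those diverted to self-report. If self-report understates weight, the first route looks like extra loss among controls and dilutes a benefit, while the second hides gains among intervention patients and inflates it. The planned data cannot separate either from the treatment effect unless the source is known. Body weight is the first outcome named in the primary purpose.

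**Working it through.** **1. Source of weight by type of patient** (centre weights always subject to consent to forwarding)

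| Patients | Group | Baseline | 6 and 12 months |
|---|---|---|---|
| mHealth centre, accepts app, attends stay | Intervention | Centre | Centre |
| mHealth centre, accepts app, misses stay | Intervention | Centre | Self-report |
| mHealth centre, declines app, attends stay | Control | Centre | Centre |
| mHealth centre, declines app, misses stay | Control | Centre | Self-report |
| Control centre | Control | Centre | Questionnaire sent, hence self-report |

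Both groups contain both sources, in proportions that the article does not give. In completer analysis (b), restricted to patients with three stays, the intervention group has attended both follow-up stays, so its self-report row drops out while control-centre patients are still followed by questionnaire. The contrast is sharpest there.

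**2. Size of the bias.** Let d be the mean under-reporting in kg, and pC and pI the self-reporting shares among controls and intervention patients. The spurious between-group difference in change is d × (pC − pI), in favour of control when positive. If the error differs by group, it is dC × pC − dI × pI, whose sign is open.

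**3. The plan's own figure.** Inputs from Sampling and participants: η² = 0.01, α = 0.05, power 0.80, r = 0.30, three occasions, two groups. Then f² = 0.01/0.99 = 0.0101 and λ = f² × N × 3/(1 − r) = 0.0101 × 225 × 3/0.70 = 9.74. With 2 and 446 degrees of freedom, power is 0.802. N = 225 reproduces, and 225/(1 − 0.50) = 450. These figures are not at fault.

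**4. The bias on the same scale.** A spurious offset of 0, b, b SD over the three waves gives λ = (N/4) × (2/3) × b²/(1 − ρ) = (N/6) × b²/(1 − ρ). Setting this equal to the planned λ, N and ρ cancel: b = √(18 × 0.0101) = 0.43 SD. The planned effect is thus equivalent to a step of 0.43 SD.

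**5. Illustration.** The article gives no weight SD, self-report error or self-report share. Assumed: SD 20 kg, d = 2 kg, N = 225 in equal groups, no true effect, weight tested alone. The correlations 0.90 and 0.95 are assumptions for body weight; 0.30 is the plan's.

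| Self-report, control / intervention | Net offset | False-positive rate at ρ = 0.30 / 0.90 / 0.95 |
|---|---|---|
| 100% / 0% | 2.0 kg = 0.10 SD | 9% / 39% / 69% |
| 100% / 30% | 1.4 kg = 0.07 SD | 7% / 21% / 38% |
| 70% / 30% | 0.8 kg = 0.04 SD | 6% / 10% / 15% |

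The nominal rate is 5%. Against the planned step of 0.4264 × 20 = 8.53 kg, these offsets are 2.0/8.53 = 23%, 1.4/8.53 = 16% and 0.8/8.53 = 9%. Varying d from 1 to 3 kg and the SD from 15 to 25 kg widens the range. In the mildest case (70%/30%, 1 kg, SD 25) the rates are 5.1%, 5.7% and 6.5%. In the most severe (100%/0%, 3 kg, SD 15) they are 23.8%, 94.3% and 99.9%.

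**The case against.** The strongest reply is that the confounding is partial. A reader might infer that self-report error affects the control group only. The documents do not support that: intervention patients who miss a stay also self-report, and patients who decline the app at mHealth centres are controls on the stay-based schedule. This stands, and it is why the net offset, not the gross shift among controls, is what counts.

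A reader might also take it as settled that every control-centre patient self-reports. That follows from where the questionnaires go, but the article does not say it of weight, and two of these centres offer return stays where a centre weight could be obtained. No provision for doing so is stated.

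The article asks for light clothing, no shoes and precision to 0.1 kg, and its Discussion concedes that procedures differing between centres may confound the effect. The first standardises conditions without making the source the same; the second is general and does not mention outcome measurement. Recording the source and adding sensitivity analyses may properly be left to a fuller document, but the unequal procedure is fixed in this text.

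One might extend the point to the questionnaires, completed during a stay by some and at home by others. The documents give no basis for any size of such an effect, so no claim is made here.

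Finally, self-selection into groups and differences in length and number of stays are larger, acknowledged sources of confounding. A uniform weight source would not make the contrast causal. This bears on the severity, not on whether the asymmetry exists.

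**Conclusion.** The point holds in limited form and should be fixed. As written, the source of follow-up weight is unequal between groups and partly determined by the outcome, and no listed covariate separates it from the group-by-time effect. Its size and net sign are unknown: under the assumptions shown, the distortion runs from negligible to serious, depending on the self-report shares, the reporting error and the within-patient correlation of weight. The mechanism rests on the text alone; the numbers rest on the stated assumptions. The sample size is unaffected.

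**What to change.** 1. Add one self-reported weight item to the questionnaire for all patients in both groups at all three waves, completed before weighing where patients are weighed.
2. Record the source and date of every weight.
3. Obtain centre weights from the two control centres with return stays where those stays fall near 6 and 12 months. The article gives no interval for these stays, so this must be checked; otherwise a difference in source is exchanged for one in timing.
4. Prespecify a same-source analysis of weight, with self-report in both groups, beside the main one. Use paired values to estimate the self-report error. State that follow-up pairs come mainly from stay attenders, who are selected for not having gained weight, and that a report made in the centre may differ from one made at home.

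An analysis limited to assessments made at attended stays is not a substitute, because attendance depends on not having gained weight.

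The cost is slightly longer forms and coordination with two sites. Patients already enrolled may lack a paired baseline value.

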#### Global physical activity questionnaire

Physical activity will be assessed with the Global Physical Activity Questionnaire (GPAQ) [30]. The GPAQ consists of 16 items measuring volume and intensity of moderate and vigorous intensity in the areas of work, transport, and discretionary time. Moreover, the GPAQ measures daily sedentary time. The GPAQ has been shown to have a 10-days test-retest reliability of *r* = .83 to *r* = .96 and a 3-months test-retest-reliability of *r* = .53 to *r* = .83 [31]. The GPAQ also shows a moderate agreement with accelerometer measures [32].

#### Healthy eating style

Healthy eating style will be measured with the 12-item questionnaire (HESQ) assessing food consumption patterns [33]. The questionnaire has a seven-point Likert scale from strongly disagree (1) to strongly agree (7). In a previous study, this scale had an acceptable reliability of Cronbach᾽s α = 0.77 and showed an adequate one-factor solution [33].

#### Dutch eating behaviour questionnaire

The Dutch Eating Behaviour Questionnaire (DEBQ) will be used to assess different eating styles associated with obesity [34]. The DEBQ consists of 30 items, including three different subscales: restraint eating, emotional eating, and external eating. Each subscale has 10 items and the responses are given on a five-point Likert scale from never (1) to very often (5). A previous study has shown Cronbach᾽s α = 0.92 for restraint eating, α = 0.94 for emotional eating and α = 0.89 for external eating [34]. In addition, scores in both the emotional eating and external eating subscales have been shown to be higher in individuals with obesity [34]. For this reason, only these two subscales will be used in the present study.

#### SF-12

The SF-12 will be used to measure health-related quality of life [35]. The SF-12 consists of 12 items with continuous and dichotomous response formats, which comprise the two dimensions physical and mental health. Studies have shown Cronbach᾽s α = 0.87 for mental health and α = 0.83 for physical health [35]. The SF-12 was shown to be applicable independent of the current health status [36] and to be associated with other indicators of physical and mental health [37].

#### Positive and negative affect schedule

The Positive and Negative Affect Schedule (PANAS) short form [38] will be used to measure emotional well-being as one aspect of health-related quality of life. This questionnaire consists of the two subscales positive affect and negative affect, each measured by five items. The patients will be asked to what extent they generally feel these affective states on a five-point Likert scale, ranging from not at all (1) to extremely (5). The 8-weeks test-retest reliability of the short-form was *r* = .84 [38]. The positive affect subscale was shown to have a positive association with subjective well-being, and the negative affect subscale was shown to have a negative association with subjective well-being [38].

#### Behavioural regulation exercise questionnaire-2

The Behavioural Regulation Exercise Questionnaire-2 (BREQ-2) [39] will be used to measure motivational regulation. The questionnaire consists of 19 items with a five-point Likert scale, ranging from not true at all (1) to very true (5). The BREQ-2 measures five dimensions of motivation: intrinsic motivation, identified regulation, introjected regulation, extrinsic motivation, and amotivation. The reliability has been shown to range from acceptable to good (α = 0.73 − 0.86) for the different dimensions [39]. In addition, the subscales representing more autonomous types of motivation were shown to be positively associated with health behaviours [40].

#### Intention

Intention will be assessed with a two-items questionnaire, namely whether the individuals will intend and whether they will be sure to be physically active [41]. The answers will be given on a seven-point Likert scale, ranging from totally disagree (1) to totally agree (7). The Cronbach’s α of this scale was at 0.83 in a previous study [41].

#### Self-efficacy

Self-efficacy will be assessed with a questionnaire specifically related to self-efficacy towards physical activity (SSA-scale) [42]. The questionnaire consists of twelve items with a five-point Likert scale, ranging from not sure at all (1) to very sure (5). The questionnaire has a Cronbach’s α of 0.89 and was shown to distinguish between physically active and inactive individuals [42].

#### PACES

An adapted short-form of the Physical Activity Enjoyment Scale (PACES) will be used to assess the individuals’ enjoyment in relation to physical activity [43]. In this study, we will use those four items that focus on the subjective experience of enjoyment (e.g., “I find physical activity pleasurable”). The PACES has been shown to be related to the physical activity levels of individuals [43].

#### Habit

Habit will be assessed with the Self-Report Behavioural Automaticity Index (SRBAI) [44]. The SRBAI consists of four items with a seven-point Likert scale, ranging from strongly disagree (1) to strongly agree (5). Cronbach’s α has been shown to be between 0.86 and 0.88 [45]. Moreover, the SRBAI has been shown to have a positive association with physical activity [44].

#### Data collection of qualitative study

Semi-structured interviews will be conducted with ten to fifteen patients of the mHealth obesity intervention group. A purposive sampling [46] will be used to recruit (a) patients who are still active in the mHealth obesity intervention and (b) patients who had dropped out of this intervention. When providing informed consent for the study, patients are additionally asked if they would also like to be interviewed. Because patients should have sufficient experience with CASPAR for the interview, patients who agreed to the interview will be contacted after the second measurement (i.e., after they have had approximately six months of experience with CASPAR). Interview guidelines will be developed to target applicability, acceptance, and usability of the mHealth intervention. A specific focus will be on the emotional difficulties patients have in changing their behaviour. To ensure a natural flow of the interview, the order of the questions may vary depending on the patients’ responses [46]. In addition, patients will be encouraged to talk about personally relevant issues not directly related to the research questions. The interviews will last about 30 min and will be conducted via Skype or phone.

### Data analysis

#### Data analysis of quantitative data

All data related to personal information will be pseudo-anonymized. Data will be entered by a research assistant and checked independently for their accuracy by another research assistant. Multiple imputation or the full-information maximum likelihood approach will be employed to treat missing data [47]. We will conduct two analyses: (a) with all patients who agreed to participate in the intervention and (b) with only those patients who completed the intervention (i.e., they had three stays at an obesity centre). A multivariate analysis of variance with repeated measurements (2 groups x 3 time points) will be used to analyze the effects of the intervention on the dependent variables (i.e., body weight, physical activity, eating style & behaviour, health-related quality of life). For the analysis of the structure of determinants of physical activity (i.e., motivation, intention, self-efficacy, enjoyment, habit) and its interdependencies, structural equation modeling procedures will be applied. In particular, the development of the dependent variables will be analyzed using latent growth curve models [48]. Moreover, mediation analyses will be conducted to test whether the determinants of physical activity mediate the effects of the intervention on physical activity behaviour. The effects of age, gender, frequency of participation in the mHealth application (supplied by the provider), and the physical activity level outside of the intervention will be controlled.

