### Methods

#### Sampling and participants

The patients are recruited from obesity centres across Germany. Currently, the participants will be recruited from seven obesity centres and it is possible that more obesity centres will participate. Of the seven obesity centres, four offer an mHealth intervention and three do not. The inclusion criteria are that patients are at least 18 years old, have a basic knowledge of the German language, and a BMI ≥ 30. During their first stay at the obesity centre, patients will be asked to participate in the study. Due to the nature of the study, neither participants nor staff can be blinded to allocation. Thus, patients attending an obesity centre that offers an mHealth intervention will be asked whether they want to take part in the mHealth intervention. The patients who agree to take part in such an intervention will be assigned to the intervention group, while those who do not want to take part in such an intervention will be assigned to the control group. Moreover, patients attending a obesity centre that does not offer mHealth interventions will be assigned to the control group. The patients will receive no financial compensation for their participation in the study.

Given the insufficient evidence for the effectiveness of mHealth obesity interventions [28], a small effect size was considered in the power analysis. Conservatively estimating the effect size by *η*^2^ = 0.01, *α* = 0.05, 1-*β* = 0.80, with two groups, a correlation on among repeated measures of *r* = .30 and a design with three repeated measurement occasions, using an ANOVA with repeated measurements (within-between interaction), the calculated total sample size is 225 participants, nearly equally distributed over two groups. Since we expect a dropout rate of about 50% [29], the plan is to recruit 450 patients.

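### One of the two permitted missing-data methods, full-information maximum likelihood, is not available for the planned repeated-measures MANOVA, so with about 50% dropout expected the effectiveness test could fall back to complete cases

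*Protocol article*

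**What the plan says.** All references are to the protocol article.

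- **Data analysis of quantitative data.** On missing data: "Multiple imputation or the full-information maximum likelihood approach will be employed to treat missing data". The text does not say which method goes with which analysis. The intervention effects on body weight, physical activity, eating and quality of life are assigned to a repeated-measures MANOVA with two groups and three time points. The same paragraph adds that "the development of the dependent variables will be analyzed using latent growth curve models". Two analysis sets are named: everyone who agreed to the intervention, and those who completed all three stays.
- **Abstract, Methods.** The MANOVA and the growth curve models are named together for comparing the two groups.
- **Sampling and participants.** The sample size of 225 was obtained "using an ANOVA with repeated measurements (within-between interaction"). The recruitment target then follows: "Since we expect a dropout rate of about 50" per cent, 450 patients are to be recruited.
- **mHealth obesity intervention.** A further stay is conditional on not having gained weight since the last one.
- **Quantitative data collection methods.** At mHealth centres, follow-up takes place at the second and third stays. Questionnaires are also sent to patients of these centres who "do not attend them (e.g., due to weight gain, another stay was not approved by the insurance provider"), with a reminder after two weeks. Patients of the other centres receive questionnaires at six and twelve months.
- **Body weight.** Patients who are not at the centre are asked to report their own weight.

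**The concern.** The choice between the two missing-data methods is not free for every analysis that follows. FIML suits the growth curve and structural equation models. It is not an estimator for a conventional repeated-measures MANOVA, which needs each outcome at each of the three time points for every patient included. If FIML were chosen, two analyses of the same dependent variables would rest on different patients: the growth models on everyone with data, the MANOVA on complete cases.

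This would matter less if little were missing. Here half the sample is expected to leave, and attendance at mHealth centres depends partly on the outcome. Patients who gain weight may lose the next stay, and with it the weight supplied by the centre, and then depend on returning a questionnaire. If gainers return fewer questionnaires, and if this happens more in one group than in the other, a complete-case comparison would be biased. The MANOVA and the growth models could then disagree for reasons unrelated to the intervention.

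**Working it through.** **1. The plan's own figures.** Inputs from Sampling and participants: η² = 0.01, α = 0.05, power 0.80, r = 0.30, three occasions, two groups. With f² = 0.01/0.99 = 0.0101, the within-between interaction has

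λ = f² · N · m / (1 − r) = 0.0101 × 225 × 3 / 0.70 = 9.74, df1 = (3 − 1)(2 − 1) = 2, df2 = (225 − 2) × 2 = 446.

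The noncentral F gives power 0.802, and N = 225 is the smallest total that reaches 0.80. Dropout: 225 / (1 − 0.50) = 450. Both figures reproduce.

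**2. What a complete-case MANOVA would retain.** 450 × 0.50 = 225 at most, which is what the study was sized on. There is no power loss at that point, but no margin either. A patient also leaves if any one scale is incomplete at any one time point. For assumed complete-case totals, the same formula gives:

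| Complete cases | Power |
|---|---|
| 450 | 0.98 |
| 225 | 0.80 |
| 180 | 0.70 |
| 158 | 0.64 |
| 113 | 0.49 |

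**3. Possible bias in kg.** None of these inputs is in the document. Assume no true effect, a six-month change of N(−3, SD 6) kg, later change with mean 0 and independent of it, 12-month weight observed in 30% of intervention patients who gained and 60% of the others, and random dropout in controls.

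- P(gain) = P(Z > 0.5) = 0.3085
- Share observed = 0.3085 × 0.30 + 0.6915 × 0.60 = 0.5075
- Contribution of gainers to the mean = −3 × 0.3085 + 6 × 0.3521 = 1.187; of the others = −3 − 1.187 = −4.187
- Complete-case mean = (0.30 × 1.187 − 0.60 × 4.187) / 0.5075 = −4.25
- Bias = −4.25 − (−3.00) = −1.25 kg, favouring the intervention

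With 40%/55% observed the bias is −0.63 kg; with 20%/64% it is −1.84 kg.

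**4. Sensitivity to the one-arm assumption.** If a share s of controls followed the same pattern as the intervention arm and the rest dropped out at random at the same overall rate, the bias would be −1.25 × (1 − s). At s = 0.5 it is about −0.6 kg, and at s = 1 it is zero.

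**5. Second illustration, in SD units.** No true effect, 225 per arm, about 50% missing at 12 months, missingness driven by six-month change in the intervention arm only, correlation 0.30 to 0.95. The complete-case difference is −0.06 to −0.36 SD. A likelihood estimate that uses the six-month value is within 0.01 SD of zero. With the same mechanism in both arms, the complete-case difference is about zero.

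**The case against.** A reader might infer that the plan discards every incomplete patient and that its main analysis is therefore a completer analysis selected on weight. The document does not support this, for four reasons.

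- Multiple imputation is named first, can precede a MANOVA and would keep incomplete patients. The natural pairing is imputation for the MANOVA and FIML for the growth and structural equation models. Only the second analysis set is a completer set, and it is openly declared as one.
- The MANOVA is not labelled the main analysis. The Abstract also names growth curves for the group comparison, and these can use all available data.
- A missed stay is not missing data. Non-attenders at mHealth centres are mailed, reminded and asked for their weight, so what changes first is the source of the weight. That gainers respond less often is plausible but not stated.
- Patients who decline the digital programme at mHealth centres are controls with the same follow-up route, so selection need not be confined to one arm.

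These points stand and limit the claim. It is also fair that pooling rules and sensitivity analyses are commonly left to a statistical analysis plan, and that imputation using the six-month weight would remove the illustrated bias as well as a likelihood model would. What remains is narrower: the text allows a choice in which one of the two options does not work with the test it names.

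**Conclusion.** The point holds in a limited form. As written, the plan permits FIML as the missing-data method alongside a MANOVA that cannot use it. On that branch the effectiveness test becomes a complete-case analysis of at most about 225 of 450 patients, while the growth and structural equation models use all of them. On the imputation branch this does not happen.

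The stated sample size and power are correct and are not in question. The risk is bias, and its size cannot be derived from the document. The −0.6 to −1.8 kg range rests entirely on assumed values: the distribution of weight change, lower response among gainers, selection in the intervention arm only and random dropout among controls. It should not be read as an estimate for this trial, and it shrinks to zero if both arms share the mechanism. The change is worth making because it costs little and removes the dependence on which branch is chosen.

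**What to change.** Make a likelihood-based linear mixed model with group × time, fitted per outcome, the effectiveness analysis, using every patient with any data. This also matches the univariate group × time test behind the sample size. If the MANOVA is kept, commit to multiple imputation for it, state the pooled test (for example a Wald test of group × time on the pooled coefficients), and reserve FIML for the growth curve and structural equation models.

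In either case, record the reason for each missed stay. Add one delta-adjusted sensitivity analysis in which missing weights are shifted above the model prediction, for example by +1 to +5 kg, since neither likelihood nor standard imputation protects against missingness that depends on the unobserved weight.

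Cost: a change of analysis wording, one data field and modest extra analysis work, with no additional patients. The mixed-model route gives up the single omnibus multivariate test.
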